***Views towards intervention***						
Exit interview	-	Self-report	Acceptability of randomized controlled trial			x

#### Feasibility of study procedures

The time taken to complete measurements at each home visit will be recorded, to document the feasibility of study procedures. We will assess the feasibility of measuring outcomes listed in Table 1 and amend measures should participants experience difficulties in completing them. Recruitment and attrition rates will be recorded.

#### Demographics

Self-reported sex, age, postcode, ethnicity and education will be recorded.

#### Health, physical functioning and wellbeing

Physical health will be assessed objectively via blood pressure measurements, taken using an Omron M2 Classic monitor (Omron Healthcare, Kyoto, Japan), over the unclothed upper arm. Physical functioning will be objectively assessed via performance on a short battery of tests, including walking speed, hand grip strength (using a Jamar Hydraulic Hand Dynamometer; Patterson Medical, Warrenville, IL), chair rises and standing balance, which assess balance, gait, strength and endurance. Wellbeing will be self-reported using the EQ5D visual analogue scale [57]. Fall history in the year prior to baseline, and during the treatment period, will be self-reported using a single item derived from the Fall Risk Assessment Tool [58]. Confidence in balance will be self-reported using the CONFBal scale [59], and fear of falling will be self-reported using the international version of the Short Falls Efficacy Scale [60]. Fatigue will be self-reported using two items taken from the Center of Epidemiological Studies Depression Scale that assess the frequency with which, over the past week, ‘everything you did felt like an effort’ and ‘you could not get going’ [61]. Severity of general pain and stiffness over the previous week will each be self-reported using a single verbal descriptor item [62].

#### Behaviour measures

Among the intervention group, adherence to each of the activities recommended in the booklet will be self-reported on ‘tick sheets’ for eight weeks post-baseline. Participants will be requested to return tick sheets to the research team either by post in prepaid envelopes or at the 8-week follow-up visit.

Generic physical activity and sedentary behaviour will be self-reported using a short form of the International Physical Activity Questionnaire [51] and a validated sedentary behaviour questionnaire [52], and objectively measured over three 7-day periods using activPAL3 accelerometers (PAL Technologies, Glasgow, Scotland). These devices are lightweight, do not provide physical activity feedback to wearers, and are sensitive to transitions between sitting, lying down (both sedentary behaviours) and standing (a physical activity), so can distinguish true sedentary behaviour from inactivity [63]. Data on total sitting time, physical activity (step count, cadence (speed) of steps), and sit-to-stand transitions during each wear period will be entered into analyses.

Devices will be pre-programmed to begin data collection on the day following their fitting, and participants’ unique identifier codes will be programmed into each unit to facilitate data matching. The activPAL device will be fitted to the participant’s thigh, with the same thigh used for all wear periods, using a waterproof dressing to allow showering and bathing as normal.

#### Psychological measures

Habit strength for generic physical activity and sedentary behaviour and, in the intervention group only, each of the behaviours recommended in the tips will be assessed using a single automaticity item, adapted to each focal behaviour. This item (‘(Behaviour X) is something I do without thinking’) is derived from the automaticity subscale of the Self-Report Habit Index (SRHI) [64, 65]. A single item was chosen on the basis of data emerging from the preliminary field test that suggest that participants struggle to understand SRHI items, or show understandings that deviate from those intended by researchers. The chosen item has shown satisfactory content and predictive validity, and convergent validity with its parent index [64].

#### Experiences of the study

At the final measurement session, all participants will be interviewed about their experiences of the study. Topics will focus on convenience and acceptability of study procedures, potential for burden arising from participation, favourability towards the allocated leaflet, and potential behavioural and associated changes arising from the leaflet. This information will be used to document intervention acceptability and feasibility of study procedures, and, in the intervention group, experiences of habit formation.

### Data management, analysis and dissemination

#### Data management

All data will be generated and curated according to University College London procedures on data recording, storage and backup protocol. Data will be collected and entered into a database by the lead researcher ([name]). Only the lead researcher and chief investigator (BG) will have access to the data, which will be stored in a password-protected database on a secure shared network at University College London accessible to [name] and BG. To maintain confidentiality, personal data will be stored in a separate data file from all other study data. With the exception of consent forms, all personal data will be destroyed when data collection has been completed. Hand-completed consent forms and questionnaires will be stored in a locked filing cabinet in a locked office at University College London for five years after the trial ends, in line with institutional data storage policy.

#### Analysis of primary outcomes

The number of participants recruited in each month of the study, and the number attending each of the home visits, will be reported for each group. Differences in attrition rates between the two arms at each time-point will be explored using Chi-square tests, and reasons for drop-out, where available, will be reported.

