### Exploratory trial

#### Study design

An exploratory two-arm pilot RCT will be undertaken to evaluate the intervention. Participants will be randomized to receive either the habit-based booklet (intervention condition), or an existing UK National Health Service (NHS) fact sheet on physical activity and sedentary behaviour in older adulthood (control condition). Assessments will be made at baseline, and 8 and 12-weeks post-baseline (follow-up). Participants will be blinded to condition, but owing to staffing constraints, the researcher administering the intervention will be required to obtain outcome measures, so will be unblinded. Primary outcome measures will be recruitment and attrition rates, and secondary outcome measures will be changes in behaviour, habit, health and wellbeing. The study was registered on the International Standard RCT Number (ISRCTN) Register^a^ (ISRCTN47901994) in January 2014. The trial start date differs from that stated on the ISRCTN Register (April 2014) because of multiple unforeseen delays. The new planned start date is September 2014, and the trial is scheduled to end in February 2015. Recruitment had not begun at the time of submission of this manuscript.

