#### Study setting

Participants (*n* = 120) will be identified through general practices in Barnet and Enfield, boroughs in north London, UK, chosen because of the high percentage of older adults (≈15%). The sample size has been pragmatically determined, to obtain sufficient data to capture variability and inform a power calculation for a larger-scale definitive RCT, while minimizing trial costs [49]. Consent will be obtained at the general practice, and data collection and treatment administration undertaken in participants’ homes.

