**Participant flow.**

Study information packs will be sent by post by the practice to a random sample of at most 300 eligible patients, with additional mail outs conducted if response rates among the first 300 are low (below 20%). The study pack will contain a study invitation letter, information sheet and business reply envelope. All documents within the pack will feature unique codes that identify the practice and recipient number, permitting calculation of response rates. Both the invitation letter and information sheet will list eligibility criteria for consideration for entry into the study. A tear-off sheet for return to the research team will be provided, so that interested patients can self-report their eligibility, contact details and consent to be contacted further by the research team.

Those who return the tear-off sheet will be phoned by a research team member, and asked to confirm their age and retirement status. Patients’ physical capability will be assessed by asking them to confirm that they could comfortably participate for at least 10 consecutive minutes in a set of physical daily activities, chosen to cover stretching, strengthening, balance and aerobic activities, each of which feature in the intervention booklet (for example, walking, housework). Patients will self-report their physical activity and sedentary behaviour over the telephone, using an adapted and validated short form of the International Physical Activity Questionnaire, which documents daily activity and sitting [51], and measures of time spent in specific sitting-based activities [52]. Patients confirmed as eligible will be invited to an appointment with a researcher at the general practice, at which they will provide written consent. Patients will be asked to bring their invitation letter to this session, to allow recording of per practice recruitment rates. A baseline measurement and treatment administration session will be arranged to take place a week later at the participant’s home. Recruitment to baseline is due to cease in December 2014, owing to time constraints.

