### Randomization

Participants will be block randomized to study conditions, using a 1:1 allocation ratio, according to a random number list, computer-generated using specialist software by an independent trial administrator. Randomization will occur between the consent session and the first (baseline) home visit. After completing the consent session, the researcher will phone the trial administrator, who will consult the random number list to allocate the participant to a condition. A unique identification code denoting the participant and the participant’s general practice will be allocated by the trial administrator, to permit matching of data across time points.

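### The primary outcomes are analysed as monthly recruits by arm and low-powered chi-square tests, when recruitment per pack mailed and attrition with confidence intervals would inform the definitive trial better at no extra cost

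*Protocol article*

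**What the plan says.** Under Study design the protocol article states: "Primary outcome measures will be recruitment and attrition rates". Analysis of primary outcomes then fixes how they are handled. Two sets of counts, "The number of participants recruited in each month of the study, and the number attending each of the home visits", are to be given separately by arm. For attrition, "Differences in attrition rates between the two arms at each time-point will be explored using Chi-square tests", with reasons for drop-out reported where known. That section names no denominator for recruitment, no pooled attrition figure and no interval estimate.

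Other sections bear on this:

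- **Recruitment procedure: patients.** Packs carry practice and recipient codes, "permitting calculation of response rates". Patients bring the invitation letter to the consent session so that recruitment can be recorded by practice.
- **Feasibility of study procedures.** Recruitment and attrition rates are to be recorded.
- **Randomization.** "Randomization will occur between the consent session and the first (baseline) home visit". Allocation is blocked, 1:1.
- **Study setting.** The target is 120 participants. "The sample size has been pragmatically determined, to obtain sufficient data to capture variability and inform a power calculation" for the later definitive trial.

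**The concern.** A feasibility trial should hand the definitive trial two planning quantities: how many people must be approached to randomise one, and what share of those randomised will be lost. Each is a proportion and needs a denominator and a measure of uncertainty.

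The stated analysis does not lead there directly. Arm is assigned after consent, so recruits by arm describe the allocation list rather than the feasibility of recruiting. Recruits per month depend on effort, and effort is designed to vary. One practice per borough opens in the first month, with up to seven in all, and further packs are mailed where response to the first 300 is below 20%. A change in the monthly count could reflect mailing volume alone.

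For attrition, the only inferential method named is a test of the arm difference. If that test is weak at this sample size, its result tells the planners of the next trial very little, while overall attrition, which they need to inflate their sample size, is not named as an output.

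**Working it through.** **Inputs from the article.** Total 120, allocation 1:1, hence 60 per arm. First mail-out of at most 300 packs (read as per practice), at most seven practices. Expected response 30%.

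**Assumptions.** Two-sided 5% level. Attrition between 10% and 25%, because the article gives no expected attrition.

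**The plan's own figures.** The 120 is described as pragmatic and has no stated inputs, so it cannot be re-derived. The yield can: 10% × 40% = 4% of registered patients eligible, and 4% × 30% = 1.2%, given as 1%. That agrees after rounding. These planning figures are proportions of people eligible or approached, so only a proportion can check them. A count per month cannot.

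**Recruitment.** Suppose all seven practices mail 300 packs: 7 × 300 = 2,100. If 120 are randomised, the yield is 120/2,100 = 5.7% (Wilson 95% CI 4.8% to 6.8%). Apply that constant yield to mailing effort:

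- two practices mailing in one month: 600 × 0.057 ≈ 34 recruits
- five practices mailing in one month: 1,500 × 0.057 ≈ 86 recruits

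The monthly count rises 2.5-fold with no change in willingness to take part. The mailing pattern is hypothetical.

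**Power of the chi-square test.** Exact enumeration of the uncorrected Pearson test over all pairs of binomial outcomes with n = 60 per arm. The last column is the usual two-proportion formula for 80% power, n = [1.96√(2p̄(1−p̄)) + 0.84√(p₁(1−p₁)+p₂(1−p₂))]² / (p₂−p₁)², where p̄ is the mean of p₁ and p₂.

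| Attrition, arm 1 v arm 2 | Power at 60 per arm | n per arm for 80% power |
|---|---|---|
| 10% v 20% | 33% | 199 |
| 15% v 25% | 28% | 250 |
| 20% v 30% | 25% | 294 |
| 25% v 35% | 23% | 329 |
| 10% v 25% | 58% | 100 |

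With a continuity correction, the first two rows fall to 25% and 20%. Reaching 80% power at 60 per arm takes a true difference of about 20 points from a 10% base and about 25 points from a 25% base.

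**What estimation gives from the same data.** Wilson intervals for pooled attrition, n = 120:

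| Observed attrition | 95% CI | Half-width (points) |
|---|---|---|
| 10% | 5.8% to 16.7% | 5.4 |
| 15% | 9.7% to 22.5% | 6.4 |
| 20% | 13.8% to 28.0% | 7.1 |
| 25% | 18.1% to 33.4% | 7.7 |

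For the arm difference, with equal observed attrition of 20% in each arm, the Newcombe 95% CI is ±14.3 points.

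**An example.** If 6/60 and 12/60 drop out, χ² = 120 × (6×48 − 12×54)² / (60 × 60 × 18 × 102) = 2.35, p = 0.13. The difference is 10 points with a Newcombe 95% CI of −3 to 23. The interval shows that a 20-point gap has not been excluded. The p-value does not.

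**Low attrition.** An expected count below 5 arises when pooled attrition is under 5/60 = 8.3%. Enumerated type I error of the uncorrected test is 5.0% at 8% attrition, 4.6% at 5%, about 3.5% at 3% and 1.9% at 2%. The test holds its level and then becomes conservative.

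**The case against.** The case for the plan is substantial. The article does make rates obtainable: packs are coded, per-practice recruitment is recorded, and recruitment and attrition rates are listed among the feasibility measures. Recruits per month is itself a rate over time and is useful for scheduling a later trial. Attendance by group, set against numbers randomised, gives attrition by arm and, by addition, overall. The tests are only to be explored, in a pilot of pragmatic size, and no decision hangs on them. A journal article may leave intervals to a fuller protocol or SAP, which is not shown here.

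Most of this stands, and it limits the point. A reader might infer that the plan yields no recruitment rate. The sections on patient recruitment and on feasibility of study procedures contradict that. A reader might also infer that the chi-square approximation breaks down when few drop out. The enumerated type I error does not bear this out. Nor does the article say that a non-significant test will be taken as equal retention. The absence of intervals would be a weak point taken alone.

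What the objection leaves unanswered is that the section on primary outcomes does choose an analysis, and a better one is available from data already planned. Its by-arm recruitment split carries almost no information about feasibility, and the only inferential method it names has low power for attrition gaps of a plausible size. Splitting by arm is harmless as a denominator for attrition, but it is not a recruitment result.

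**Conclusion.** The point holds as an improvement to a stated analysis. It is not a claim that the primary outcomes cannot be obtained. The analysis fixed for them does not use the denominators the article collects, splits recruitment by an allocation made after consent, and rests inference about attrition on a test with 33% power (10% v 20%) or 28% (15% v 25%) for a 10-point difference. Power is lower still from higher base rates. The same 120 participants would give overall attrition to within about 5 to 8 points.

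These figures assume 60 per arm actually randomised, a two-sided 5% level and attrition of 10% to 25%. The yield of 5.7% further assumes 2,100 packs mailed. Other attrition rates would change the figures, but over this range the conclusion that estimation serves better than the test does not change. The consequence is moderate: the data remain recoverable, but the trial's headline results would be reported in a less useful form than they could be.

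**What to change.** Reword Analysis of primary outcomes as follows.

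1. **Recruitment.** Report number randomised divided by packs mailed, and also divided by responders and by those confirmed eligible by telephone. Give each overall and per practice with a 95% CI (Wilson, for example), and do not split by arm. Monthly recruits can stay as a description, shown with the practices open and packs mailed that month.
2. **Attrition.** Report the proportion of those randomised without 8-week and 12-week data, overall and by arm, and the arm difference, each with a 95% CI. Keep reasons for drop-out.
3. **Chi-square tests.** Drop them, or keep them as secondary to the intervals.

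The cost is analysis wording only. The pack codes, invitation letters, telephone screening and visit records already planned can supply the denominators, and recruitment had not begun when the article was submitted. If a fuller protocol or SAP already specifies these estimates, a cross-reference from this section is enough.

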#### Analysis of secondary outcomes

Analyses of changes in secondary outcomes (physical activity, habit, wellbeing, physical health, functioning) will be run using valid data at all three time points to analyze changes among completers only. Non-completers will be accounted for by using last-observation-carried-forward and baseline-observation-carried-forward analyses, the latter to ensure a more conservative assessment of potential changes in outcomes. Between-group changes in outcomes over the first 8 weeks will be assessed using *t* tests, and within-group changes examined using repeated measures analysis of variance (ANOVA). To evaluate whether habit change is associated with behaviour change, we will calculate correlations between changes in automaticity for generic physical activity and sedentary behaviour (and, in the intervention group, for each target habit), and changes in physical activity within each group. Effect sizes for changes in self-reported physical activity will be used to inform a power calculation to determine the sample size required for a definitive RCT. Qualitative interview data will be analyzed using thematic analysis.

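### Baseline-observation-carried-forward is not ensured to be conservative for the between-arm difference, and the completers rule leaves usable 8-week data out

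*Protocol article*

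**What the plan says.** All of this stands in the protocol article under Analysis of secondary outcomes, unless another section is named.

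- Analysis set: the secondary analyses "will be run using valid data at all three time points to analyze changes among completers only".
- Missing data: "Non-completers will be accounted for by using last-observation-carried-forward and baseline-observation-carried-forward analyses, the latter to ensure a more conservative assessment", which the sentence ties to changes in outcomes. No other method is named.
- Between-arm test: "Between-group changes in outcomes over the first 8 weeks will be assessed using *t* tests". Change within each arm is examined by repeated measures ANOVA.
- Downstream use: effect sizes for self-reported physical activity go into the sample size of a definitive trial. Study setting gives the same purpose for the pilot: "The sample size has been pragmatically determined, to obtain sufficient data to capture variability and inform a power calculation for a larger-scale definitive RCT". The section does not say whether the completers, LOCF or BOCF analysis supplies these effect sizes.
- Timing: Study design and Table 1 place outcome measurement at baseline, 8 weeks and 12 weeks. The 4-week contact is a phone call (Study procedure), so baseline is the only value before week 8.
- Attrition: it is a primary outcome and is compared between arms by chi-square (Analysis of primary outcomes).

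**The concern.** The text says that BOCF will ensure conservatism. That can hold for change within an arm. For the difference between arms it depends on how many people each arm loses and on how far each arm moves, and neither is known in advance.

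Unequal loss is foreseeable, since the protocol plans to test for it. Only intervention participants have tick sheets, ten extra habit items and an offer of support at the 4-week call. Non-zero change in both arms is also plausible: the Discussion allows that the control fact sheet may work about as well as the booklet. With a September start, baselines until December and an end in February, a winter decline in both arms is possible too.

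The completers rule raises a second issue. The between-arm test concerns the first 8 weeks, yet this analysis requires week-12 data as well, so it omits people whose 8-week change was observed.

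The stake is the effect size handed to the definitive trial. If it comes from a distorted analysis, that trial may be planned too small or too large.

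**Working it through.** **Inputs.** From the protocol: n = 120 allocated 1:1, so about 60 per arm; measurements at 0, 8 and 12 weeks; t test on change to week 8. The protocol gives no dropout rate, mean change, SD, alpha or power, so there is no figure of its own to reproduce. All such values below are assumptions.

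**1. Bias of BOCF.** Let μI and μC be the true mean improvements, and dI and dC the proportions without a value at the visit analysed, with dropout unrelated to outcome within each arm.

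BOCF difference = (1 − dI)μI − (1 − dC)μC

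Bias = BOCF difference − (μI − μC) = dC·μC − dI·μI

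| μI, μC (min/day) | dI, dC | True difference | BOCF difference |
|---|---|---|---|
| 30, 30 | 10%, 25% | 0 | 27 − 22.5 = 4.5 |
| −30, −30 (both worsen) | 25%, 10% | 0 | −22.5 + 27 = 4.5 |
| 40, 20 | 10%, 25% | 20 | 36 − 15 = 21 |
| 40, 20 | 20%, 20% | 20 | 32 − 16 = 16 |
| 40, 20 | 25%, 10% | 20 | 30 − 18 = 12 |

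BOCF can therefore create, slightly enlarge or clearly shrink the difference. Within one arm it gives (1 − d)μ, which is always closer to zero.

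**2. Effect on a later sample size.** In units of the SD of change, take true changes 0.5 and 0.3, a difference of 0.20. BOCF variance per arm is (1 − d) + d(1 − d)μ².

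At dropout 10% and 30%:
- BOCF difference: 0.9 × 0.5 − 0.7 × 0.3 = 0.24
- Variances: 0.9 + 0.09 × 0.25 = 0.9225 and 0.7 + 0.21 × 0.09 = 0.7189
- Standardised effect: 0.24 / √0.8207 = 0.265

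With n per arm = 2(1.960 + 0.842)²/effect² (two-sided 5%, 80% power), the true 0.20 needs 393 per arm and 0.265 needs 224. At 20%/20% the BOCF effect is 0.176 (508 per arm), and at 30%/10% it is 0.088 (2037 per arm). These sample sizes use unrounded effects.

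**3. Week 8.** For anyone without a week-8 value, the last observation is the baseline, so LOCF and BOCF insert the same number. With true changes 0.5 and 0.3 (now in units of the outcome SD), overall dropout 10% and 30%, and half of it before week 8, both give 0.95 × 0.5 − 0.85 × 0.3 = 0.220.

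**4. Simulation.** 60 per arm, 4000 runs, within-person correlation 0.6, half of dropout before week 8.

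- True difference 0.20, dropout 10%/30% unrelated to outcome, week 8: completers 0.198; all available week-8 data 0.200; LOCF and BOCF both 0.220.
- No true difference, both arms improving 0.4, dropout 10%/30%: false positives with BOCF are 6.3% at week 8 and 8.4% at week 12. At 10%/40% they are 7.0% and 13.7%.
- No true difference, poor responders leaving the intervention arm only (nominal dropout 30%/10%), change to week 8: completers 0.31 with 41% false positives; all available week-8 data 0.123 with 10%; LOCF and BOCF 0.064 with 6.4%.

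The mixed model itself was not simulated; the all-available comparison stands in for it.

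**The case against.** The protocol's wording concerns changes in outcomes and is relative to LOCF. For change within an arm, BOCF does what the text says. It also shrinks the between-arm difference when dropout is equal, or higher in an intervention arm that improves more. This stands: only the promise to ensure conservatism fails, and only for the between-arm difference. A reader might infer that BOCF is never conservative; the working above contradicts that.

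A reader might also infer that all three analyses are biased whenever dropout rates differ. That is not so. Unequal rates alone leave the completers comparison unbiased (0.198 against 0.20); bias there needs dropout that relates to outcome.

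Nor does the protocol name the completers analysis as the main one. The loss of 8-week data from people who miss only week 12 applies to that analysis, because LOCF keeps their observed week-8 values.

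Two further inferences lack support. That single imputation makes the standard errors too small was not shown here: the excess false positives for carry-forward arise where its estimate is itself biased. And if 10% of accelerometer wear periods were invalid, independently, a rule requiring all three would keep 0.9³ = 73% of participants (61% to 86% for 15% to 5%). That is lost precision on accelerometry, not bias in the self-reported effect size meant for the power calculation.

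Finally, the primary outcomes do not depend on imputation, and attrition is reported by arm, so an unequal pattern would be visible. This also stands, and it limits the severity.

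**Conclusion.** The point holds in a limited form. BOCF is not ensured to be conservative for the between-arm difference, and for the planned 8-week test it is no more conservative than LOCF for people without a week-8 value. The completers version leaves out observed 8-week data and is open to bias if dropout relates to outcome.

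The size rests entirely on assumed inputs. In the illustrations the spurious effect is 4.5 min/day, a true 20 min becomes anything from 12 to 21 min, and a later trial that needs 393 per arm could be planned at 224 or at 2037. At week 8 the inflation of false positives is small (6.3% to 7.0% in the cases tried).

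The distortion may reach the power calculation; it is not certain to, because the protocol does not say which analysis feeds it. The outcomes are secondary and the trial is an exploratory pilot, so this should be changed but does not threaten the primary aim.

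**What to change.** 1. Make the main secondary analysis a linear mixed model on all randomised participants with any follow-up value, with baseline, arm, visit and arm-by-visit terms, under missing at random. Report the 8-week arm contrast from it. People seen at week 8 but not at week 12 then contribute.
2. State that the effect size for the definitive trial's power calculation comes from this model.
3. Keep the completers analysis and, if wanted, LOCF and BOCF as labelled sensitivity analyses.
4. Delete the claim that BOCF ensures a conservative assessment where the between-arm difference is concerned.
5. Treat multiple imputation with a delta shift for dropouts as optional. It needs a shift for each arm across many outcomes, some of them single items, and the protocol offers no basis for choosing one.

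The cost is revised wording and a little more programming, with no new data. The trial had not begun at publication, so the change could be made before any outcome is seen. The downside is reliance on missing at random: in the simulated case where poor responders left one arm, the all-available comparison was still biased (0.123), and more so than carry-forward (0.064). That is a reason to keep sensitivity analyses beside the model.
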